#### Follow-up telephone call

Between 7 and 14 days after the end of the last study period, the absence of untoward medical or mental sequelae of the study will be ascertained in a follow-up telephone call with the subject.

### Sample size {14}

Given the rationale of improving preclinical to clinical translation of pain effects and the intention to use these biomarkers in future early clinical pharmacology studies, a robust signal in a small number of subjects is required if this biomarker is to prove useful in early drug development. In fact, if the investigated drugs and measured effects do not show robust (i.e., significant primary) biomarker signals on the basis of several tens of subjects, the overall usefulness of this biomarker is rather limited. Therefore, the following illustration of the estimated power of this study with a range of 10 to 30 subjects (in total) should serve as justification for the (evaluable) sample size to be chosen at 12 overall (preferably at one center with additional centers providing data for reliability testing at similar sample sizes).

Knowledge on the variability and effect sizes of EEG parameters are available with tramadol versus placebo as treatment in healthy subjects [27], with alfentanil versus baseline in healthy subjects [26], as well as before versus after morphine treatment in chronic pain patients [32]. The study by Truini et al. [27] conveys effects (i.e., group differences of the LEP N2-P2 changes relative to baseline) around 60% (placebo group) and 90% (tramadol group), i.e., a 30% group difference. The provided data by Petersen-Felix et al. [26] suggests standard deviation (SD) parameters for LEP peak-to-peak amplitude of the negative-positive vertex to be around 25%. With the tapentadol versus placebo comparison of the primary analysis (on LEP peak-to-peak amplitude relative changes from baseline, 2-sided type I error of *α*/2 = 0.025) being essentially a paired *t* test with assumed correlation of 0.3, the power graph shown in Fig. 3 yields 12 evaluable subjects in total to be a reasonable sample size for at least 85% power. While this appears sufficient for the primary analysis, data for similar numbers of subjects would be recommended from all centers for test-retest reliability investigations. Therefore, sample sizes of 8 to 12 subjects treated for all four study periods are required in each participating center.

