## Statistical methods

### Statistical methods for primary and secondary outcomes {20a}

This and the following sections briefly specify the statistical analysis principles for the study. Final and detailed specifications on the quantitative analyses described here will be provided correspondingly in the statistical analysis plan to be finalized prior to unblinding of the study.

The general level of significance used is *α* = 5% (two-sided). However, this will only be considered as confirmatory within the multiplicity adjusted statistical analysis of the primary endpoints and the key secondary endpoints.

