#### Statistical procedure

The statistical procedure for the selected, confirmatory analyses will follow the sequentially rejective multiple testing approach described by Bretz et al. [42]. The two primary endpoints (LEP N2-P2 amplitude change at non-sensitized arm and PEP N2-P2 amplitude change at sensitized arm) will be tested for their differences between the treatment arms tapentadol versus placebo, first. This will be conducted in parallel, splitting the overall *α* equally between the two endpoint tests, i.e., each test has a type I error of *α*/2. If any of these two tests shows significant differences, key secondary analyses will be conducted using the *α*-levels as passed on from initial/prior tests according to specified weights. The exact procedure (with the local levels as well as the weights with which to pass *α*-levels on) is shown in Fig. 5, and related specifications are provided in the subsequent subsections.

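### The stated power of at least 85% with 12 evaluable subjects does not follow from the plan's own inputs, which give 80.5%; a minor correction, since the pooled four-centre analysis is amply powered

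*Protocol article*

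**What the plan says.** All inputs stand in the protocol article, section Sample size {14}.

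- Effect: changes in the LEP N2-P2 amplitude of "around 60% (placebo group) and 90% (tramadol group), i.e., a 30% group difference", taken from a published tramadol study.
- Variability: SD parameters for "LEP peak-to-peak amplitude of the negative-positive vertex to be around 25" per cent, taken from a published alfentanil study.
- Test: the tapentadol versus placebo comparison is described as "being essentially a paired *t* test with assumed correlation of 0.3".
- Level: "2-sided type I error of *α*/2 = 0.025". This agrees with the section Statistical procedure, where "each test has a type I error of *α*/2", and with the overall two-sided level of 5% under Statistical methods {20a}.
- Result: the power graph in Fig. 3 "yields 12 evaluable subjects in total to be a reasonable sample size for at least 85% power".

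The caption of Fig. 3 again names a paired t test for a mean difference, with power plotted against the number of pairs. The same section then asks for 8 to 12 completers in each participating centre, for test-retest reliability work.

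**The concern.** The section gives everything needed to repeat the calculation: difference, SD, correlation, level, test and number of pairs. At least 85% is a floor, so a result clearly below it means that the written inputs and the written result disagree.

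The figure matters because it is the formal justification for choosing 12 evaluable subjects overall. For an analysis of exactly 12 subjects, the chance of missing the planned effect would be about 20% (100 − 80.5 = 19.5%), where the text implies at most 15%. Anyone who reuses the calculation for a later single-centre biomarker study of that size would carry the error over.

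**Working it through.** **Inputs** (all from Sample size {14})

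- Difference δ = 90 − 60 = 30 percentage points
- SD = 25 percentage points, read as the SD of the percentage change within each treatment period
- Correlation between periods ρ = 0.3
- Two-sided α = 0.025
- Paired t test, n = 12 pairs, df = n − 1 = 11

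**Calculation**

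1. SD of the paired difference = SD × √(2(1 − ρ)) = 25 × √1.4 = 29.58.
2. Standardised difference = 30 / 29.58 = 1.014.
3. Noncentrality at n = 12: 1.014 × √12 = 3.513.
4. Critical value, t with 11 df, upper tail 0.0125: 2.593.
5. Power from the noncentral t distribution: **80.5%**. A simulation of 400,000 trials gave 80.6%.

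**Power by number of pairs, same inputs**

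| Pairs | Power |
|---|---|
| 12 | 80.5% |
| 13 | 84.6% |
| 14 | 88.0% |

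The smallest number of pairs with at least 85% power is 14.

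**Attempts to reproduce at least 85% at n = 12**

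| Variant | Power | Agreement with the text |
|---|---|---|
| Two-sided α of 0.05, not split | 89.1% | Contradicts the stated 0.025 |
| Normal approximation, α 0.025 | 89.8% | Not a t test with 11 df |
| 25 read as the SD of the difference | 92.2% | Makes the stated correlation redundant |
| Four-period mixed model, 30 residual df | 86.9% | Close to the planned analysis, but not the test named |

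The 30 residual df come from 12 subjects in four periods: 48 observations − 12 subjects − 3 for treatment − 3 for period = 30.

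Fig. 3 is not available in the text reviewed, so which of these, if any, lies behind the 85% cannot be settled.

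**Power of the analysis as planned**

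Study setting {9} names four centres. With 8 to 12 completers in each, the total is 4 × 8 = 32 to 4 × 12 = 48. The paired t test on the same inputs gives 99.94% at 32 and more than 99.99% at 48.

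**The case against.** **The inputs are rounded.** The text gives the effects and the SD as approximate, calls the test essentially a paired t test and presents the exercise as an illustration. At 12 pairs, 85% is reached with an SD of about 23.6, a difference of 32 or a correlation of about 0.38. This stands as a reason to treat the gap as small. It does not make the sentence correct, because the stated values do not give the stated floor.

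**The planned model delivers the figure.** The section Primary analysis of primary endpoints specifies a mixed model with compound symmetry. With 12 completers its 30 residual df give 86.9%. The common variance that this needs is exactly what compound symmetry assumes, so it is a fair basis for the claim. What remains is a mismatch: both the text and the Fig. 3 caption name a paired t test on pairs, and neither mentions pooled degrees of freedom.

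**The consequence does not reach the trial as designed.** This stands in full. The primary tests use the full analysis set, which contains all randomized subjects, with centre as a fixed effect. Nothing in that section restricts them to 12 subjects or to one centre.

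Three stronger inferences are tempting, and the documents support none of them:

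- *A reader might infer that the trial has a 20% chance of missing its planned effect.* That holds only for an analysis of exactly 12 subjects, not for the 32 to 48 completers planned.
- *A reader might infer that the plan's reading of a null result is undermined.* The Sample size section ties limited usefulness to the absence of a robust signal in several tens of subjects, not in 12. At that size the power on these inputs is high.
- *A reader might quote the power at zero correlation (64.0% at 12) or at 8 subjects (54.5%).* The documents give no correlation other than 0.3, so the first is conjecture. The 8 is the lower end of a per-centre number set for reliability testing, not for a primary test within a centre.

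**Conclusion.** The sentence is wrong as written. On the plan's own inputs, 12 evaluable subjects give 80.5% power, 4.5 points below the stated floor of 85%, and 14 are needed to reach it. This rests on the nominal values, on reading 25 as the SD of the percentage change in each period, and on the paired t test that the text and the Fig. 3 caption both name.

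It is a minor error in the stated justification and not a flaw in the design. The sample that enters the primary analysis is well beyond 14, and the planned mixed model would itself support a figure above 85% at 12 subjects if the text said that this was the basis.

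**What to change.** Change the one sentence in Sample size {14}, in either of two ways:

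- State the paired t test result: *12 evaluable subjects give about 80% power (paired t test, two-sided alpha 0.025); 14 are needed for at least 85%.*
- Or keep the claim of at least 85% and give its basis: *the four-period mixed model with compound symmetry, 30 residual degrees of freedom with 12 completers, power 86.9%.* The description of the test and the Fig. 3 caption should then be changed to match.

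If Fig. 3 was drawn with other values, state the alpha, SD, correlation and degrees of freedom used. A further sentence noting that the primary analysis pools about 32 to 48 completers would show the power of the test that will actually be run.

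The cost is wording only. No subjects are added, and the design, the endpoints and the analysis do not change.

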**Fig. 3 Fig3:**
[figure not shown]
Power as a function of number of pairs (paired *t* test for mean difference)

A potentially high dropout rate and missing data needs to be taken into consideration given the complexity of the design and procedures. This is already addressed by the analysis approach, but to compensate for potentially 20% dropouts, a total of 12–16 subjects will be enrolled per participating center (in the sense of randomizing subjects to enter the treatment phase).

As mentioned above, in case significant signals are not found in this study as conclusion, this is already valuable information for the broader objective of the trial. It should also be noted that the insights into the characteristics of the investigated drugs and biomarkers (cf. PK/PD analyses and/or test-retest reliability) also contribute to the trial rationale irrespective of any significant finding in the primary analysis.

### Recruitment {15}

Healthy subjects will be recruited by advertisements on webpages, newspapers, university billboards, etc. The recruitment rate is anticipated to be 3–4/month per center. Subjects will be pre-screened to identify subjects who could potentially be enrolled into the trial.

#### Screen failures

Screen failures are defined as subjects who consent to participate in the clinical trial but are not subsequently randomly assigned to the IMP. A minimal set of screen failure information is required to ensure transparent reporting of screen failure subjects, to meet the Consolidated Standards of Reporting Trials (CONSORT) publishing requirements and to respond to queries from regulatory authorities. Minimal information includes demography, screen failure details, eligibility criteria, and any serious adverse event (SAE).

#### Subject discontinuation from the trial

Once a subject enrolls in the trial, whilst protecting subject safety, the trial site will make every effort to retain the subject for the planned duration of the trial. A subject may withdraw consent at any time. This will automatically lead to discontinuation of the subject from the trial. The investigator will discontinue the subject’s participation in the study if further participation would involve unjustifiable risk to the subject’s mental or physical well-being or if participation would be against the purpose and interest of the study.

In general, subjects who discontinue are those who complete the end of trial earlier than the end of study period 4. Subjects who discontinue their participation in the trial will not be replaced. The Principal Investigator will document on the case report form (CRF) any discontinuation of a subject and inform the sponsor. Where applicable, the relevant IEC(s) must be informed with a detailed written explanation.

The following will be done for all discontinued subjects, including those who withdrew informed consent:
Document the main reason for discontinuation from the trial.Ensure that all data collected until the time of discontinuation is transferred to the CRF.Complete any other trial-related formalities, e.g., those related to discharge from the trial site.For subjects withdrawing consent, document in the source data the date and time of withdrawal.If a subject withdraws consent and agrees (documented in writing) conduct the follow-up telephone call.

### Assignment of interventions: allocation

#### Sequence generation {16a}

All four study periods of the trial will be double-blinded.

Lacosamide, pregabalin, tapentadol or placebo will be assigned to each subject by a double-blind randomization schedule.

Randomization will be by site. At the first study period day before first IMP administration, subjects will be randomized to receive the lowest available randomization number at the site.

The randomization list (per site) will be built in blocks of four “4-period sequences,” these sequences being random permutations of the four 4-period sequences of a (basic) Latin square. Each block (allowing the sequential allocation of four participants) will use an own (new) random permutation of the Latin squares’ four rows.

The basic Latin square will be chosen randomly from a selection of the 24 available, cf. Table 5.1 in Senn [33], namely the Williams squares therein, with the constraint that each medication precedes each other medication once in this Latin square.

If two (or more) basic Latin squares are used, e.g., permuted rows of the first for randomization of the initial four participants and the permuted rows of the second for the subsequent four participants, then the choice of Latin square per block will also be made randomly.

#### Concealment mechanism {16b}

Each IMP will be administered overencapsulated as single oral dose (two capsules).

A sealed decoding envelope per treatment period will be provided for each randomization number. Each envelope will contain the identification of the IMP allocated to that subject.

#### Implementation {16c}

The IMPs lacosamide (Vimpat®), tapentadol (Palexia®), and pregabalin (Lyrica®) will be purchased centrally by the Heidelberg University Hospital Pharmacy. The pharmacy will perform the manufacturing of placebo capsules and the overencapsulation of the IMPs Lyrica, Palexia, and Vimpat. The IMP will be packaged and labeled centrally by the pharmacy and will be in compliance with applicable local regulations. Detailed information about the packaging and labeling is laid down in a specification document (available on request) with written instructions on, for example, processing, labeling, packaging, quality control, release, storage, and/or delivery of the IMP. The allocation sequence and sealed envelopes will be generated by the Heidelberg University Hospital Pharmacy.

Storage conditions will be specified on the labels of the IMPs according to applicable EU and local regulation. The IMPs will be stored in a secure place with restricted access and temperature monitoring. The IMP delivery (shipping), return, and disposal will be performed in accordance with the specification document (available on request). Controls will be implemented at the trial site to ensure documented compliance with these requirements.

As tapentadol is one of the IMPs in this study, all sites need to be licensed according to local law for the receipt, storage, handling, and administration of narcotics.

General unblinding will only take place after the trial has been completed and the database is locked. Except for single-subject unblinding in emergency situations, investigator unblinding will only be carried out after database lock. Unblinding will be performed by the statistician.

## Assignment of interventions: blinding

### Who will be blinded {17a}

The investigator/trial personnel and subjects will be blinded to the assignment of pregabalin, tapentadol, lacosamide, and placebo (double-blind procedure).

The personnel analyzing the plasma samples for PK analysis will be unblinded during the bioanalytical analysis, but will supply their data to the trial database in a blinded fashion.

### Procedure for unblinding if needed {17b}

The investigator will receive appropriate methods for single case unblinding (i.e., sealed decoding envelopes per treatment period for each randomization number which contain the individual treatment assignment).

Each envelope contains the identification of the IMP allocated to that subject. The investigator may only break the code (open the envelope) when it is necessary and in the subject’s interest to identify the IMP given (e.g., if knowing the identification of the treatment would lead to the investigator treating the subject differently).

For every subject whose blinding code was broken, the following information will be documented:
The reason for, the date, and time of unblinding.The person performing the unblinding.The persons informed of the treatment allocation/randomization.

In order to maintain the double-blind nature of the trial, the allocated treatment for a subject will not be communicated further unless required for the surveillance of the subject or, if necessary, for urgent risk to benefit re-evaluation and/or measures for urgent risk minimization. If required by local regulations, it may be that the IEC needs to be informed.

## Data collection and management

### Plans for assessment and collection of outcomes {18a}

#### Collection of pharmacokinetic data

Venous blood samples will be collected at the scheduled time-points (detailed in Table 5) after drug administration and will be used to determine drug plasma concentrations to be used for PK modeling and subsequent PK/PD analysis.

An overview of the total amount of blood to be collected from each study participant is provided in Table 6. In each study period, 5 blood samples, 6 mL each, will be drawn into tubes containing K2-EDTA as anticoagulant and will be centrifuged within 30 min after collection. The harvested plasma will be frozen at − 20 to − 80 °C within 1 h of sampling and kept frozen until sent for analysis. Detailed descriptions of the sample procurement and processing will be provided in a separate specification manual. Bioanalysis will be performed by ESTEVE using validated methods.

**Table 6 Tab6:** Overview of blood sampling volumes during the study

	Volume / sample (mL)	Number of samples	Total volume (mL)
Screening visit	6	1	6
Optional visit	6	1	6
Pharmacokinetics:			
Period 1	6	5	30
Period 2	6	5	30
Period 3	6	5	30
Period 4	6	5	30
Maximum total volume of blood per subject (mL):			132

#### Collection of demographic data and other baseline characteristics

##### Demographic data

Demographic data to be collected and recorded for this trial are age, sex, body weight, and height.

##### Prior and concomitant medication

All medication requiring prescriptions (including oral contraceptives) and/or over-the-counter medication used within 10 days prior to enrollment and up to the end of the trial will be recorded. Any change in dosage, regimen, or route, during the study will be recorded as a new entry.

##### Relevant prior/concomitant disease or surgical interventions

Current medical conditions and conditions within the last 7 days and controlled by medication will be recorded. Childhood illnesses do not need to be documented, unless they are considered to potentially affect the assessment of the biomarker or could potentially give rise to an adverse event based on the pharmacology of the IMP or related to trial procedures.

##### Physical examination

At the screening visit, a focused neurological examination will be performed in the presence of any clinically evident sensory disorder.

##### Electrocardiography

At screening, a 12-lead electrocardiogram (ECG) will be recorded in supine position after at least 10 min rest. Electrodes will be positioned in accordance with the recommendations of the American Heart Association: three cycles 12-lead ECG and simultaneous rhythm strip at 25 mm/s with a gain setting of 10 mm/mV. The ECG will specifically be checked for signs of 2nd or 3rd degree atrioventricular (AV) block (exclusion criterion, contraindication for lacosamide).

##### Urine pregnancy test

At screening and at the beginning of each study period, a urine pregnancy test will be performed using suitably validated methods commonly used at the site.

##### Alcohol consumption check

At screening and at the beginning of each period, abstinence of consumption of alcohol will be checked.

##### Urine drugs of abuse test

At screening and at the beginning of each period, urine samples provided by the subject will be tested for the presence of opiates, amphetamines, and cannabinoids using suitable validated methods commonly used at the site. This is to avoid that tapentadol (tapentadol has μ-opioid activity) is administered to subjects who have recently taken substances with relevant CNS depressant activity as this may increase the risk of sedation (safety risk if the subject leaves the site, negative impact on study results), dizziness (safety risk), and respiratory depression (safety risk).

